## Abstract

**Background:**

Whether acupuncture is effective for relieving perimenopausal syndrome has been controversial recently. In this article, we report the protocol of a randomized controlled trial using acupuncture to treat perimenopausal syndrome, aiming to answer this controversy.

**Design:**

A multicenter randomized controlled trial with two parallel arms is underway in China. Two hundred and six women with perimenopausal syndrome will be randomly assigned to a treatment group using acupuncture plus auricular acupressure (AA group) and a control group using Climen® (Bayer Healthcare Company Limited, Guangzhou, China), a 28-day sequential hormone replacement therapy, in a 1:1 ratio. Participants in the AA group will receive three acupuncture sessions per week in the first 4 weeks and two sessions per week in the following 8 weeks, for a total of 28 sessions over 12 weeks. Auricular points will be plastered by Semen Vaccariae twice per week for a consecutive 12 weeks, with both ears used alternately. The Climen® control group is prescribed a tablet containing estradiol valerate 2 mg/day for the first 11 days, and a tablet containing estradiol valerate 2 mg/day plus cyroterone acetate 1 mg/day for the following 10 days. The total treatment period of the control group is three cycles. The post-treatment follow-up period will last 24 weeks. The primary outcome is the Menopause Rating Scale (MRS) assessed at baseline and 4, 12, 16, 24 and 36 weeks after randomization. The secondary outcomes are Menopause-Specific Quality of Life, average hot flash score during 24 hours, serum estradiol, follicle-stimulating hormone and luteinizing hormone level. The first two secondary outcomes are measured at the same point as the MRS. Other secondary outcomes are measured at baseline and 12, 24 weeks after randomization.

**Discussion:**

The results of this trial, which will be available in 2015, will clarify whether acupuncture is effective to relieve perimenopausal syndrome.

**Trial registration:**

ClinicalTrials.gov NCT01933204 (registered 9 August 2013)

## Background

Perimenopause is defined as a period during 2 to 8 years preceding menopause and 1 year after final menstruation [1]. During this period, the changes in serum hormone levels – especially estrogen – cause perimenopausal syndrome, manifested as menstrual irregularities, hot flashes, sweats, insomnia, emotional disorders, vaginal dryness, sexual dysfunction, and so forth. The syndrome significantly reduces the women’s health-related quality of life [2,3]. Hormone replacement therapy (HRT) is an effective method to relieve these symptoms [4]. According to recent studies, however, HRT may increase the risk of coronary heart disease [5], stroke [6], breast cancer [7], and endometrial cancer [8]. The benefits of estrogen plus progestin are unable to counterbalance the risks, indicated by the Women’s Health Initiative [9]. More and more women therefore seek alternative therapies rather than HRT, because of the life-threatening side effects [10,11].

As one of the complementary and alternative therapies without serious side effects [12,13], acupuncture is used frequently to treat a wide range of health problems [14], including hot flashes, which is one of the most common symptoms and the reason why women in the stage of menopausal transition seek medical care [15]. However, several randomized controlled trials (RCTs) indicated that acupuncture is not superior to sham acupuncture in relieving perimenopausal symptoms [16-19]. Reliable and valid evidence for the effectiveness of treating perimenopausal syndrome with acupuncture is still inadequate, due to the number, size, design scheme, and quality of recent studies. We therefore designed a multicenter RCT to address these problems, anticipating providing a more conclusive answer to these questions.

In this trial we primarily aim at investigating whether acupuncture is effective and safe in treating perimenopausal syndrome through a comparison with HRT. This work reported in this article is financed by the National Key Technology R&D Program during the Twelfth Five-year Plan Period of China, and is registered with identifier NCT01933204 by ClinicalTrials.gov in the USA.

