## Method and design

### Study design

This study is a multicenter RCT comparing an acupuncture plus auricular acupressure (AA) treatment group with a Climen® (Bayer Healthcare Company Limited, Guangzhou, China) control group (Figure 1, Table 1). Two hundred and six participants will be included from the following three hospitals in Chengdu, Sichuan, China: First Affiliated Hospital of Chengdu University of Traditional Chinese Medicine (TCM), Chengdu Integrated TCM & Western Medicine Hospital, and General Hospital of Chengdu Military Region of the Chinese People’s Liberation Army.

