**Figure 1 F1:**
[figure not shown]
**Trial flow chart.** CPA, cyroterone acetate; E_2_V, estradiol valerate. Climen® from Bayer Healthcare Company Limited (Guangzhou, China).

**Table 1 T1:** Trial processes chart

	**Baseline**	**Treatment phase**			**Follow-up phase**		
	**Week −1**	**Week 0**	**Week 4**	**Week 12**	**Week 16**	**Week 24**	**Week 36**
Patients							
Enrollment	×						
Informed consent	×						
Signed informed consent		×					
Medical history	×						
Physical examination	×		×	×			
Laboratory test	×			×		×	
Breast and gynecological ultrasound	×			×			
Randomization		×					
Expectation of acupuncture		×					
Intervention							
Acupuncture plus auricular acupressure treatment group (*n* = 103)			28 sessions of acupuncture				
Comparison							
Climen® control group (*n* = 103)			E_2_V 2 mg/day for days 1 to 11 and E_2_V 2 mg + CPA 1 mg/day for days 12 to 21				
Outcomes							
MRS		×	×	×	×	×	×
MENQOL		×	×	×	×	×	×
Average hot flash score during 24 hours		×	×	×	×	×	×
Serum estradiol, FSH and LH levels	×			×		×	
Patients’ satisfaction			×	×			
Trial evaluation							
Safety of acupuncture			×	×			
Cost–benefit analysis				×			
Reasons of drop-outs or withdrawals							×
Patients’ compliance							×
Adverse events							×
Medicine alliance							×

CPA, cyroterone acetate; E_2_V, estradiol valerate; FSH, follicle-stimulating hormone; LH, luteinizing hormone; MRS, Menopause Rating Scale; MENQOL, Menopause-Specific Quality of Life. Climen® from Bayer Healthcare Company Limited (Guangzhou, China).

These participants will be randomly assigned to two groups (AA treatment group and Climen® control group) through central randomization in a 1:1 ratio. The central randomization system will be used and performed by the Clinical Evaluation Center of China Academy of Chinese Medical Sciences in Beijing. Authorized researchers can obtain random numbers and group assignments by calling the central randomization service number or logging into the website to apply. This procedure assures that randomization will not be influenced either by the acupuncturist or the patients.

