### Acupuncture plus auricular acupressure treatment group

All acupoints are punctured by filiform needles when patients are lying in a comfortable supine position. Sterile, disposable Hwato needles (provided by Suzhou Hwato Medical Instruments Co. Ltd, Suzhou, China) are used in this study; they are 25 to 50 mm in length and 0.30 mm in diameter. The needle is inserted with the double hand-needle insertion technique. The depth of insertion is adjusted based on the standard permissible depth of insertion for each acupoint. The needle is then twirled, rotated, lifted and thrust moderately until achieving De qi sensation. The needles are retained for 30 minutes in every session and manipulated twice every 10 minutes with intermittent stimulation. Each manipulation lasts for 10 seconds. All needles are taken out with clean cotton balls to avoid bleeding after 30 minutes. Every patient will receive 28 sessions of acupuncture in total over a period of 12 weeks: three sessions per week in the first 4 weeks, every 2 days with a 1-day interval; and two sessions per week in the following 8 weeks, every 3 days with a 2-day interval.

All of the auricular points will use plaster therapy. One piece of Semen Vaccariae is put in the middle of one piece of 0.5 cm × 0.5 cm medical adhesive plaster. After sterilizing the skin of the auricular points, the plasters are stuck to the points with hemostatic forceps. The patients are required to press the auricular points gently by themselves three to five times a day lasting 1 minute, especially pressing them half an hour before sleep for 2 minutes, until the patients have distention, soreness, numbness, and warm sensation with the local auricular skin congestive, flashed and hot. The strength of pressing should consist of the individual’s endurance. The plaster with Semen Vaccariae is exchanged for a fresh set twice weekly for 12 consecutive weeks, every 3 days with a 2-day interval, both ears used alternately.

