## Discussions

This trial is sponsored and financially supported by the National Key Technology R&D Program during the Twelfth Five-year Plan Period of China. The study reported in this article is only one part of this program, which is an international multicenter systematic evaluation of clinical effectiveness of acupuncture. The purposes of this international collaborative program are to prove the therapeutic effects and safety of acupuncture and to establish guidelines for clinical practice. The result of this trial is expected to provide convincing evidence that acupuncture is effective for patients with perimenopausal syndrome.

Previous RCTs show acupuncture in the treatment of symptoms of both perimenopausal and postmenopausal females has no advantage, compared with placebo needles [16-19]. Compared with no medical treatment (for example, self-caring, waiting), however, acupuncture is able to relieve symptoms quite well [16,17,29]. In view of controversial results, some researchers asserted that the placebo needles might have similar effects to verum acupuncture [30], and this view may underestimate the total effectiveness of verum acupuncture. We are therefore conducting a pragmatic trial that requires a positive drug as the control group to clarify an acupuncture therapeutic effect rather than a placebo needle. Moreover, we use a non-inferiority method to estimate the sample size, and only include perimenopausal patients. What we expect is to prove the therapeutic effects of acupuncture on perimenopausal syndrome, and provide another alternative treatment for perimenopausal women.

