Our study still has limitations. Firstly, the whole research period of this study is 37 weeks (1 week baseline, 12 weeks of treatment and 24 weeks of follow-up) and may increase the rate of patient drop-out. We therefore reduce the treatment demand after the first month of treatment and keep close contact with our patients via telephone calls, short messages, emails, and so forth, during the follow-up period, to decrease the drop-out rate. Secondly, the three centers of this study are in Chengdu, which is a capital city located in the southwest of China, and the patients we will include in this trial are mostly local residents. The population may therefore not represent the advantages of a multicenter study. Thirdly, participants assigned to the acupuncture group may have more opportunities for contact with their acupuncturists and build a good doctor–patient relationship rather than those of the control group, which may improve the therapeutic effect [44]. We will therefore keep close contact with patients in the control group by telephone, Internet, and so on, to decrease this potential bias. Meanwhile, it is difficult to blind patients after randomization due to the specificity of acupuncture. We therefore strictly conduct central randomization and appoint different people to perform therapy, measurement and statistical analysis.

Owing to a lack of solid evidence for effectiveness of acupuncture treatment on perimenopausal syndrome, this trial aims to clarify this issue by means of a multicenter randomized controlled large-scale trial.

In conclusion, the results of this trial are expected to confirm whether acupuncture is effective in relieving perimenopausal syndrome.

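### The aim, the non-inferiority statement and the conclusions name acupuncture, but the trial tests acupuncture plus auricular acupressure, so non-inferiority cannot be credited to acupuncture alone

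*Protocol article*

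**What the plan says.** Four places in the protocol article put the question or its answer in terms of acupuncture:

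- **Background (primary aim):** "In this trial we primarily aim at investigating whether acupuncture is effective and safe in treating perimenopausal syndrome through a comparison with HRT".
- **Abstract, Discussion:** the results "will clarify whether acupuncture is effective to relieve perimenopausal syndrome".
- **Discussions, closing conclusion:** "the results of this trial are expected to confirm whether acupuncture is effective in relieving perimenopausal syndrome".
- **Study population and sample size:** an MRS difference within 4.5 is taken to show that acupuncture is not inferior to Climen.

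The Discussions section explains the choice of control in the same terms: the trial "requires a positive drug as the control group to clarify an acupuncture therapeutic effect rather than a placebo needle".

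The design is described differently. Under Study design the trial is "comparing an acupuncture plus auricular acupressure (AA) treatment group with a Climen" control group, with women allocated "through central randomization in a 1:1 ratio". The section on the treatment group sets out a second component alongside needling, namely seed plasters on the ear points: "The patients are required to press the auricular points gently by themselves three to five times a day lasting 1 minute", and "The plaster with Semen Vaccariae is exchanged for a fresh set twice weekly for 12 consecutive weeks". The Climen group receives neither component.

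**The concern.** A two-arm trial answers a question about what differs between its arms. Here that difference is needling together with ear acupressure on one side and hormone therapy on the other. The aim and conclusions name only one of the two experimental components.

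What is at stake is the reading of a positive result. If the AA group proves non-inferior on the MRS, the article as written leads to the statement that acupuncture is effective and not inferior to Climen. The data would support that statement for the combination. They would not show whether needling without the ear component would have done as well. The Discussions section lists limitations on drop-out, the local population, contact time and blinding, but not this one, so a reader is not warned.

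**Working it through.** **1. Is acupuncture defined to include the ear component?** The rationale section first calls the regimen acupuncture plus auricular acupressure and later calls it an acupuncture protocol, which is loose shorthand. The same section and Table 3 list acupuncture points and auricular points separately. The treatment-group section describes two techniques: needles, and seed plasters that the patient presses. No definition merges the two, so a reader of the aim would take acupuncture to mean needling.

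**2. What the contrast estimates.** Write mean MRS improvement as C under Climen, N under needling alone and P under the package. Then

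P − C = (N − C) + (P − N).

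The trial estimates P − C. The aim, read literally, concerns N − C. The ear component's increment, c = P − N, is unknown. There is one estimate and two unknowns. Because no arm receives needling alone, no analysis of the between-group difference can separate them.

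**3. The plan's own sample size.** Inputs from Study population and sample size: margin 4.5, SD 10, power 90%, alpha 5% (sidedness not stated there), dropout 20%. With one-sided 0.05 and a true difference of 0:

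n per arm = 2 × (1.645 + 1.282)² × 10² / 4.5² = 84.6, rounded up to 85.

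Multiplying by 1.2 gives 102 per arm, 204 in total. This is close to the stated 103 and 206, though not identical. The calculation fixes the setting for step 4; the point itself does not depend on it.

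**4. Illustration of the consequence.** Assumptions:

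- 85 evaluable women per arm, one-sided 0.05;
- a package truly equal to Climen (P − C = 0);
- an ear increment of c MRS points, so that needling alone is worse than Climen by c. The documents give no value for c; the range is assumed.

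SE = 10 × √(2/85) = 1.534.

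Probability that the package passes = Φ(4.5/1.534 − 1.645) = 0.90, whatever c is.

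Probability that needling alone would pass in a trial of the same size = Φ((4.5 − c)/1.534 − 1.645):

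| Assumed c (MRS points) | Package passes | Needling alone would pass |
|---|---|---|
| 0 | 0.90 | 0.90 |
| 1 | 0.90 | 0.74 |
| 2 | 0.90 | 0.49 |
| 3 | 0.90 | 0.25 |
| 4.5 | 0.90 | 0.05 |

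The distribution of this trial's MRS contrast is the same in every row. A non-inferior finding therefore fits both the case in which needling alone is as good as Climen and the case in which it is worse by the full margin.

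**The case against.** The strongest reply is that this is a pragmatic trial, as the Discussions section says, and that pragmatic trials may compare a treatment package with an established drug. The combination is disclosed in the abstract, the study design, Table 1 and the intervention sections, and the arm is labelled AA. Nothing promises to separate the components. The package-versus-Climen estimate, its sample size and its analysis are unaffected.

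All of that stands, and it is why no extra arm is called for. It does not rescue the wording: a trial of a package has to state its conclusion for the package.

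A reader might infer more than the documents support:

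- **That nothing in the trial can be linked to acupuncture.** This goes too far. The adverse-event section lists bleeding, hematoma, fainting and local infection as events of acupuncture, and needle-specific events can still be tied to needling.
- **That an inferior package would say nothing about acupuncture.** If the ear component does no harm (c ≥ 0), then N − C = (P − C) − c is no better than P − C, so an inferior package would count against needling alone too. The problem lies mainly with a positive result.
- **That the relative time spent on needling and pressing shows the share of the effect.** Minutes of needle retention and minutes of pressing are unlike quantities, and neither measures effect.
- **That the margin comes from a study of needling without other components.** The sample-size section mentions only an electro-acupuncture group in an unpublished study and does not say whether anything was added to it.
- **That this trial by itself is meant to produce guidelines.** The article gives that purpose to the wider international programme, of which this trial is one part.

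**Conclusion.** The point holds as a mismatch between stated claim and design. The comparison of the package with Climen is sound in this respect. The aim, the non-inferiority statement and the conclusions are wrong as written, because they carry a result for two components over to one, and the limitations are silent on it.

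No figure in the plan changes. The size of a possible misattribution is unknown and cannot be estimated from this design. The illustrative fall from 0.90 to between 0.74 and 0.05, for an assumed increment of 1 to 4.5 MRS points, shows only how much could stay hidden behind a positive result. It rests on the assumed increment, a package exactly equal to Climen, SD 10 and one-sided 5%. If the ear component adds nothing to the MRS, the attribution would happen to be right, but this trial could not show that.

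**What to change.** State the comparison as acupuncture plus auricular acupressure versus Climen wherever the question or its answer appears:

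- the abstract (Background and Discussion);
- the primary aim in Background;
- the non-inferiority statement in Study population and sample size;
- the Discussions section, both where it explains the choice of control and in the closing conclusion.

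Add one sentence to the limitations: both components are given together and no arm receives acupuncture alone, so its separate effect cannot be inferred from a non-inferior result.

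The cost is a narrower claim. Only the text changes.

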## Method and design

### Study design

This study is a multicenter RCT comparing an acupuncture plus auricular acupressure (AA) treatment group with a Climen® (Bayer Healthcare Company Limited, Guangzhou, China) control group (Figure 1, Table 1). Two hundred and six participants will be included from the following three hospitals in Chengdu, Sichuan, China: First Affiliated Hospital of Chengdu University of Traditional Chinese Medicine (TCM), Chengdu Integrated TCM & Western Medicine Hospital, and General Hospital of Chengdu Military Region of the Chinese People’s Liberation Army.

**Figure 1 F1:**
[figure not shown]
**Trial flow chart.** CPA, cyroterone acetate; E_2_V, estradiol valerate. Climen® from Bayer Healthcare Company Limited (Guangzhou, China).

**Table 1 T1:** Trial processes chart

	**Baseline**	**Treatment phase**			**Follow-up phase**		
	**Week −1**	**Week 0**	**Week 4**	**Week 12**	**Week 16**	**Week 24**	**Week 36**
Patients							
Enrollment	×						
Informed consent	×						
Signed informed consent		×					
Medical history	×						
Physical examination	×		×	×			
Laboratory test	×			×		×	
Breast and gynecological ultrasound	×			×			
Randomization		×					
Expectation of acupuncture		×					
Intervention							
Acupuncture plus auricular acupressure treatment group (*n* = 103)			28 sessions of acupuncture				
Comparison							
Climen® control group (*n* = 103)			E_2_V 2 mg/day for days 1 to 11 and E_2_V 2 mg + CPA 1 mg/day for days 12 to 21				
Outcomes							
MRS		×	×	×	×	×	×
MENQOL		×	×	×	×	×	×
Average hot flash score during 24 hours		×	×	×	×	×	×
Serum estradiol, FSH and LH levels	×			×		×	
Patients’ satisfaction			×	×			
Trial evaluation							
Safety of acupuncture			×	×			
Cost–benefit analysis				×			
Reasons of drop-outs or withdrawals							×
Patients’ compliance							×
Adverse events							×
Medicine alliance							×

CPA, cyroterone acetate; E_2_V, estradiol valerate; FSH, follicle-stimulating hormone; LH, luteinizing hormone; MRS, Menopause Rating Scale; MENQOL, Menopause-Specific Quality of Life. Climen® from Bayer Healthcare Company Limited (Guangzhou, China).

These participants will be randomly assigned to two groups (AA treatment group and Climen® control group) through central randomization in a 1:1 ratio. The central randomization system will be used and performed by the Clinical Evaluation Center of China Academy of Chinese Medical Sciences in Beijing. Authorized researchers can obtain random numbers and group assignments by calling the central randomization service number or logging into the website to apply. This procedure assures that randomization will not be influenced either by the acupuncturist or the patients.

The total observation period within this study is 37 weeks, including 1 week of baseline, 12 weeks of treatment and 24 weeks of follow-up. After randomization, participants will receive 28 sessions of acupuncture over a period of 12 weeks plus auricular acupressure or take Climen® (from Bayer Healthcare Company Limited, Guangzhou, China) tablets for three cycles. Acupuncture will be given as three sessions weekly in the first 4 weeks and two sessions weekly in the following 8 weeks for each patient. Each session will last 30 minutes. The follow-up period will last 24 weeks (13 to 36 weeks after randomization). Patients will be assessed before randomization as well as 4, 12, 16, 24 and 36 weeks after randomization.

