During the trial, all adverse events are to be recorded during treatment and the follow-up period, including bleeding, hematoma, fainting, serious pain, local infection, and so on, caused by acupuncture; and irregular vaginal bleeding, breast tenderness, headaches, nausea, and so on, caused by Climen®. Serious adverse events associated with the trial should be reported to the principal investigator immediately. All details will be documented, treatment options for rescue will be given at once, and appropriate action will be taken to prevent recurrence.

All acupuncturists were qualified to perform this trial after they participated in special training classes and passed the examination. The special training classes were held twice in August 2013, aiming to make all of the acupuncturists well understand all details of this trial. For instance, they were trained to use the central randomization method, to fill in the case report form, to find the correct points, to manipulate the needles, and so on. Additionally, to ensure the quality of this trial, the clinical monitors will check the processes of the trial and document the details of the processes once a month in every hospital. Moreover, monitors named by the principle investigator will check the accuracy and validity of the original data from the clinical centers. Regular meetings will be held to consider the recruitment rate, adverse events, protocol violations, difficulties and problems appearing during this study, and so on.

Patient drop-outs, their reasons, and their compliance will be recorded at the 36th week after randomization. All patients will be recorded until the end of this trial.

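### Unequal contact during treatment (28 sessions against two scheduled visits) puts the safety comparison with HRT at risk of ascertainment bias, and Table 1 conflicts with the text on when adverse events are recorded

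*Protocol article*

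**What the plan says.** The Background section gives the main aim as establishing "whether acupuncture is effective and safe in treating perimenopausal syndrome through a comparison with HRT". Safety against HRT is therefore part of the question.

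The Study design section sets the contact pattern: after randomization, "participants will receive 28 sessions of acupuncture over a period of 12 weeks plus auricular acupressure or take Climen". For the AA arm: "Acupuncture will be given as three sessions weekly in the first 4 weeks and two sessions weekly in the following 8 weeks for each patient". The Climen arm takes "tablets for three cycles", and no treatment or dispensing visits are described for it. For both arms: "Patients will be assessed before randomization as well as 4, 12, 16, 24 and 36 weeks after randomization". After week 0, only weeks 4 and 12 of these fall in the treatment phase.

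On harms, the Outcome measurement section says that "all adverse events are to be recorded during treatment and the follow-up period". The events it expects in the control arm include "irregular vaginal bleeding, breast tenderness, headaches, nausea, and so on, caused by Climen". The same section gives all participants ultrasound, liver and kidney tests after treatment.

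Table 1 has a row *Safety of acupuncture*, marked at weeks 4 and 12, and a row *Adverse events*, marked only at week 36.

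The Discussions section lists as a limitation that "participants assigned to the acupuncture group may have more opportunities for contact with their acupuncturists". It treats this as something that may improve the therapeutic effect, and it promises close contact with the control group by telephone and Internet. It states neither the frequency nor the content of that contact.

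**The concern.** An adverse event enters the data only if someone learns of it. A woman who meets a trained acupuncturist every few days can mention a headache or a bruise while it is fresh. A woman on tablets with no contact between weeks 4 and 12 may have to recall it after weeks. If that happens, a side-by-side count of events or of affected women mixes true harm with opportunity to report. Transient harms of Climen would be under-counted relative to AA, and acupuncture would look less safe by comparison than it is.

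The protocol recognises the unequal contact but follows it through only for efficacy. Table 1 does not help: its treatment-phase safety row names acupuncture alone, and its general adverse-event row has no mark before week 36.

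**Working it through.** **1. The plan's own figure.** 3 sessions × 4 weeks + 2 sessions × 8 weeks = 12 + 16 = 28. The stated 28 is reproduced.

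**2. Scheduled contact in the treatment phase.** There are 28 sessions in the AA arm, against two assessments (weeks 4 and 12) in the Climen arm. AA women are due the same two assessments. 28 / 2 = 14, but this is a ratio of contacts, not of events detected.

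**3. Wait from onset to the next scheduled contact.** Assumptions (not in the documents): onset is uniform over days 0 to 84; AA gaps are 2, 2 and 3 days in each of the first 4 weeks and 3 and 4 days in each of the next 8; Climen contacts are on days 28 and 84. Mean wait = Σ(gap²/2) / 84.

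- Climen: (28²/2 + 56²/2) / 84 = (392 + 1,568) / 84 = 23.3 days.
- AA: [4 × (4 + 4 + 9)/2 + 8 × (9 + 16)/2] / 84 = (34 + 100) / 84 = 1.6 days; longest wait 4 days.
- Wait over 7 days: Climen (21 + 49)/84 = 83%; AA 0%.
- Wait over 14 days: Climen (14 + 42)/84 = 67%; AA 0%.

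**4. How far control-arm calls would change this.** Further assumptions: an event is recorded only if a contact follows within *w* days of onset, and every contact elicits events. AA sessions are placed on days 1, 3 and 5 of each week, then days 1 and 4, with the two common visits added. Share of onsets captured:

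| *w* | AA | Climen, visits only | Climen, calls every 2 weeks | Climen, weekly calls |
|---|---|---|---|---|
| 3 days | 92% | 7% | 21% | 43% |
| 7 days | 100% | 17% | 50% | 100% |
| 14 days | 100% | 33% | 100% | 100% |
| 28 days | 100% | 67% | 100% | 100% |

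The gap ranges from very large to none, depending on the recall window and on a call frequency that the article does not give.

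**5. What it could do to a risk ratio.** Assume a true risk of 20% in both arms, one event per affected woman, full capture in AA, no control-arm calls, and a fraction *f* of events with a wait over 7 days unreported. Observed Climen risk = 20% × (1 − 0.833 × *f*).

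- *f* = 0.10: 18.3%; AA:Climen ratio 20/18.3 = 1.09.
- *f* = 0.25: 15.8%; ratio 1.26.
- *f* = 0.50: 11.7%; ratio 1.71.

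The true ratio in each case is 1. These figures illustrate the mechanism and do not estimate its size in this trial.

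**6. Table 1 against the text.** The Outcome measurement section requires recording through treatment and follow-up and names expected events for both arms. Table 1 gives adverse events a single mark at week 36, 24 weeks after treatment ends, and marks treatment-phase safety for acupuncture only. The week 36 mark may mean collation at the end, as the text says for drop-outs and compliance. On that reading Table 1 still shows no adverse-event time point for the Climen arm during treatment.

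**The case against.** The best defence has five parts.

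- **A condensed article.** The wording and interval of adverse-event questions are commonly left to the full protocol. This stands as far as it goes: the missing question is not itself the fault. The point rests on what the article does state, namely the unequal schedule, a contact imbalance considered only for efficacy, and a table that disagrees with the text.
- **No statement that harms are asked about at each session.** This stands. A reader might infer that harms are caught far more completely in the AA arm and that the comparison is biased. The documents support only that this may happen. Acupuncturists are trained to fill in the case report form, so capture at sessions is possible. But therapy and measurement are given to different people, and if recording follows Table 1, both arms are assessed at the same visits.
- **Climen women have more than two contacts.** This stands. Telephone and Internet contact is planned, and step 4 shows that frequent calls that ask about harms could close the gap. Neither their frequency nor their content is fixed.
- **Symmetric safety tests.** Ultrasound and liver and kidney tests after treatment apply to both arms, so those findings are not affected. They cannot detect nausea or a headache that has passed.
- **No formal harm comparison is specified.** The Statistical analysis section names no between-arm test for adverse events, and they are not among the secondary outcomes. The stated aim is nevertheless a safety comparison with HRT, and any table of events by arm will be read as one. The per-woman loss would also be smaller than in step 5 where a complaint recurs or persists and can still be reported at week 4 or 12.

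**Conclusion.** The concern holds as a risk of bias, not as a demonstrated bias. The protocol fixes 28 sessions against two scheduled visits in the treatment phase, makes safety against HRT part of the main aim, and applies its remedy for unequal contact to efficacy alone. Detection of transient harms may therefore differ between the arms, probably to the disadvantage of acupuncture. Findings from the common laboratory and ultrasound tests are not at issue.

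The size cannot be calculated. A reader might take the ratios of 1.09 to 1.71 as an estimate of the distortion, but every input apart from the visit schedule is assumed, and the calculation sets control-arm telephone contact to zero. Nor do the documents support saying that the safety question cannot be answered at all. The disagreement between Table 1 and the Outcome measurement text rests on no assumption and needs correcting in any case.

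**What to change.** 1. Reconcile Table 1 with the Outcome measurement section. Replace the *Safety of acupuncture* and *Adverse events* rows with one adverse-event row for both arms at weeks 4, 12, 16, 24 and 36, using the same standard question.
2. Ask that question in any telephone or Internet contact with the control arm, and at matched times in the AA arm.
3. Base the main between-arm harm comparison on events elicited on this common schedule, and ask explicitly about needling-related harms such as bleeding, hematoma, fainting and pain.
4. Also report all recorded events by arm, including those noted at acupuncture sessions, with their source of detection. It may be tempting simply to leave out events noted only at sessions, but that could remove the AA arm's own needling harms and tilt the result the other way.

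The cost is small: one added question, and two adverse-event tables instead of one. The visits in item 1 are already planned for both arms. The matched questions to AA women in item 2 are a modest addition, because the article describes no such contact with them during treatment.
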